# A single-arm, open-label, intervention study to investigate the improvement of glucose tolerance after administration of the 5-aminolevulinic acid (5-ALA) in the patients with mitochondrial diabetes mellitus

**DOI:** 10.1097/MD.0000000000025100

**Published:** 2021-03-12

**Keywords:** 5-aminolevulinic acid/sodium ferrous citrate, insulin secretory capacity, mitochondrial diabetes mellitus, open-label

## Abstract

**Background::**

Mitochondrial diabetes mellitus (MDM) is characterized by maternal inheritance, progressive neurosensory deafness, insulin secretory disorder, and progressive microvascular complications. Mitochondria are critical organelles that provide energy in the form of adenosine triphosphate (ATP). An impairment of ATP production in pancreatic β cells is regarded as the main cause of the insulin secretory disorder in patients with MDM, and these patients require insulin replacement therapy early after the diagnosis. The amino acid 5-aminolevulinic acid (5-ALA), a precursor of heme metabolites, is a non-proteinogenic δ amino acid synthesized in mitochondria. An addition of ferrous iron to 5-ALA enhances heme biosynthesis and increases ATP production through an upregulation of the respiratory complex. Several studies have reported that the administration of 5-ALA and ferrous iron to existing treatment improved the glycemic control in both patients with prediabetes and those with type 2 diabetes mellitus. The additional administration of 5-ALA and ferrous iron to MDM patients on insulin therapy may improve their insulin secretory capacity and glycemic control by improving their mitochondrial function. The findings of this study are expected to provide new treatment options for MDM and improve the patients’ glycemic control and prognosis.

**Methods/design::**

This study is a single-arm, open-label pilot intervention study using clinical endpoints to investigate the effects of treatment with 5-ALA plus sodium ferrous citrate (SFC) to patients with MDM on their glucose tolerance. A total of 5 patients with MDM will be administered 5-ALA/SFC (200 mg/d) for 24 weeks. We will perform a 75-g oral glucose tolerance test before and at 24 weeks after the start of this 5-ALA/SFC treatment to evaluate glucose-dependent insulin responses.

**Discussion::**

To the best of our knowledge, this study will be the first assessment of the effects of 5-ALA/SFC in patients with MDM. This study will obtain an evidence regarding the effectiveness and safety of 5-ALA/SFC for patients with MDM.

**Trial registration::**

This study was registered with the University Hospital Medical Information Network (UMIN000040581) on July 1, 2020 and with the Japan Registry of Clinical Trials (jRCTs071200025) on August 3, 2020.

## Introduction

1

Mitochondrial diseases are heterogeneous disorders characterized by defects of energy production via oxidative phosphorylation. Endocrine dysfunction is often observed in genetic mitochondrial diseases, and among those diseases, diabetes mellitus is the most frequently described as mitochondrial diabetes mellitus (MDM). The m.3243 A>G mutation is the most common point mutation of the mitochondrial deoxyribonucleic acid (mtDNA) observed in patients with MDM. However, it might be impossible to identify the mutation of the mtDNA using the peripheral leukocytes in all patients with MDM, because heteroplasmy values show large distributions between individual tissues. It was reported that only 13.1% of the blood samples were positive for the m.3243 A>G mutation among Japanese patients with MDM.^[1]^ Generally, MDM has the following characteristics.

(1)It is maternally inherited;(2)it requires insulin therapy due to the progressive insulin secretory disorder;(3)it shows progressive neurosensory deafness; and(4)it shows rapidly progressive diabetic complications.^[1–4]^

The current recommended treatment for MDM is only insulin replacement therapy.

Mitochondria are critical organelles that provide energy in the form of adenosine triphosphate (ATP) for the insulin secretory reaction by glucose stimulation. Mitochondrial dysfunction triggers the development of diabetes mellitus by an impairment of ATP production, which is highly dependent on adequate heme synthesis.^[5]^

The amino acid 5-aminolevulinic acid (5-ALA), a nonproteinogenic δ amino acid found in the human body, promotes intracellular energy metabolism, and the addition of ferrous iron to 5-ALA enhances the biosynthesis of heme, which acts as a protein-bound prosthetic group in mitochondrial respiratory chain complexes II, III, and IV and cytochrome c. The administration of 5-ALA combined with sodium ferrous citrate (SFC) enhance heme production, leading to respiratory complex upregulation.^[6]^ Thus, 5-ALA/SFC might be effective for improving mitochondrial dysfunction and increasing the production of ATP. Treatment with 5-ALA/SFC might also improve insulin secretion by improving mitochondrial dysfunction. In fact, several studies showed beneficial effects of 5-ALA on glycemic control in both prediabetic and diabetic patients.^[7–10]^

We hypothesized that adding 5-ALA/SFC to insulin treatment in patients with MDM may improve insulin secretion and glycemic control. We, therefore, designed this study as the first step in testing the effectiveness of 5-ALA/SFC as a treatment for MDM. Herein, we describe the final study protocol (version 1.0; April 24, 2020). The results of this study are expected to provide evidence of the usefulness of 5-ALA/SFC in the treatment of patients with MDM.

## Methods/design

2

### Objective

2.1

This is a single-arm, open-label, pilot intervention study to investigate the effects of 5-ALA/SFC in patients with MDM. We created the present study design in accordance with Standard Protocol Items: Recommendations for Interventional Trials and Consolidated Standards of Reporting Trials 2010 guidelines.^[11,12]^

### Study design

2.2

The study will be conducted at the Nagasaki University Hospital in Japan. In total, 5 patients with MDM will be recruited to the study, with a 24-week duration of intervention.

### Ethical considerations

2.3

The study has been approved by the Certified Review Board (CRB) of Nagasaki University (CRB approval no.: CRB20-012) and is registered in the Japan Registry of Clinical Trials (https://jrct.niph.go.jp) as jRCTs071200025. The study will be conducted in accordance with the principles of the Declaration of Helsinki,^[13]^ Japan's Clinical Trials Act (Act No. 16 of April 14, 2017), Japan's Act on the Protection of Personal Information and related regulatory notifications, and the present study protocol.

### Study endpoints

2.4

#### Primary endpoint

2.4.1

Changes in glucose-stimulated insulin secretion after the daily administration of 5-ALA/SFC for 24 weeks. To determine the changes, the values of area under the curve of serum insulin levels from fasting (0 minutes) to 120 minutes during 75-g oral glucose tolerance test (OGTT) evaluated at 24 weeks after the administration of 5-ALA/SFC (week 24) will be compared to those at baseline (week 0).

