### Inclusion criteria

2.6

The study inclusion criteria are as follows:

(1)Patients aged ≥20 years at the time of consent(2)Outpatients(3)Patients diagnosed with MDM who satisfy all of the following main criteria and one or more of the sub-criteria

Main criteria

(1)Patients with diabetes mellitus being treated with insulin or clinically requiring insulin therapy for glycemic control due to decreased insulin secretion(2)Patients complicated with neurosensory deafness

Sub-criteria

(1)Patients who have a family history of maternally inherited diabetes mellitus(2)Patients who show a level of serum lactate ≥ 18 mg/dL (2 mmol/L) and/or a molar ratio of lactate to pyruvate ≥20(3)Patients with short stature whose height is less than –2.0 standard deviation of Japanese adults(4)Patients complicated with cardiomyopathy or cardiac conduction abnormality(5)Patients whose basal-ganglia and brainstem have bilaterally symmetric abnormal lesions on computed tomography/magnetic resonance imaging(6)Patients who have had not changed their antidiabetic agent(s) expect for insulin within 8 weeks before the informed consent is obtained(7)Written informed consent

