**Figure 1 F1:**
[figure not shown]
Treatment schedule and outcome measures. FGM = flash glucose monitoring, OGTT = oral glucose tolerance test.

After the visit date, the investigator will continue to administer 5-ALA/SFC and conduct necessary examinations and surveys until week 24 in accordance with the schedule in Figure 1. The investigator will refer to the patient's FGM result to adjust the insulin dose based on his/her own judgement. During the study period, any change of the drug or dose of antidiabetic agents (except insulin) is prohibited.

To evaluate the patients’ glucose-dependent insulin responses, a 75-g OGTT will be performed twice: before the start of the 5-ALA/SFC regimen (week 0, 1st OGTT) and at 24 weeks after the start of the 5-ALA/SFC regimen (week 24, 2nd OGTT). When patients need to be withdrawn from the study for any reason, they will undergo 75-g OGTT after discontinuing the 5-ALA/SFC. Both OGTTs will be carried out under the condition of overnight fasting. All antidiabetic agents including insulin and 5-ALA/SFC will be held until the preceding day in each OGTT.

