### Laboratory measurements

2.10

The 2 OGTTs will use a 75-g glucose formulation, Trelan-G75 (AY Pharma, Tokyo). For each OGTT, the levels of plasma glucose (mg/dL), serum insulin (μU/mL), serum C-peptide (ng/mL), and plasma glucagon (pg/mL) will be measured at fasting (0 minutes) and at 30, 60, 120 minutes after the ingestion of the glucose load. We will also measure the serum levels of glycated albumin, nonesterified fatty acid, leptin, adiponectin, high-molecular-weight adiponectin, iron, unsaturated iron-binding capacity, and ferritin at 0 minutes. Urine specimens will be obtained on each OGTT day for the measurement of the patient's albumin/creatinine ratio.

The levels of serum insulin and C-peptide will be measured by the ECLusys kit (Roche, Basel, Switzerland). Blood samples for plasma glucagon will be obtained using BD P800 tubes (BD, Franklin Lakes, NJ). Plasma glucagon will be measured by a sandwich ELISA kit (Mercodia, Uppsala, Sweden).

As shown in Figure 1, we will measure the patient's complete blood count and serum (plasma) levels of sodium, potassium, chlorine, total cholesterol, high-density lipoprotein, cholesterol, low-density lipoprotein, blood urea nitrogen, creatinine, total bilirubin, aspartate aminotransferase, alanine aminotransferase, alkaline phosphatase, γ-glutamyl transpeptidase, creatine kinase, glucose, and glycated hemoglobin at every visit of the study (week 0, 4, 8, 16, and 24), and (if withdrawing from the study) at early discontinuation.

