The administration of 5-ALA/SFC reduced blood glucose levels and improved glucose tolerance in diabetic rodents by enhancing mitochondrial function.^[18,19]^ In prediabetic and diabetic human subjects, the oral administration of 5-ALA/SFC also improved their glucose tolerance, although the dosage regimen of 5-ALA/SFC in those studies was lower than that of our present investigation.^[7–10]^ Our study could thus be expected to observe improved effects on insulin secretory capacity and blood glucose regulation by a recovery of the mitochondrial function. For the evaluation of these effect, we will perform a 75-g OGTT before and at 24 weeks after the start of the administration of 5-ALA/SFC and then compare the difference in insulin secretion.

The dosage of the investigational drug will be set at 100 mg taken orally twice daily (200 mg/d) in accord with an ongoing clinical trial for mitochondrial disease. That clinical trial was registered in the Center for Clinical Trials, Japan Medical Association (http://www.jmacct.med.or.jp) as JMA-IIA00358. Another study conducted in patients with type 2 diabetes (ClinicalTrials.gov NCT02481141) demonstrated the safety and tolerability of the dose.^[10]^ In studies using a similar dose of 5-ALA, the adverse events were consistently mild, and some studies did not observe any side effects. We consider that the 200 mg/d dose is acceptable and effective for patients with MDM.

There are some limitations in this trial.

(1)It will be conducted at a single center and the sample size is small (n = 5).(2)It is a single-arm study and lacks a placebo control group.(3)The follow-up period of the trial may be insufficient to lead to a definitive conclusion regarding the improvement of insulin secretion and glycemic control.

Despite these limitations, our research also has strengths. There has been no study assessing the effect of 5-ALA/SFC on insulin secretion and glycemic control in patients with MDM. We may discover an effective antidiabetic agent for MDM according to the pathology.

This trial will evaluate the effectiveness and safety of 5-ALA/SFC in patients with MDM. It will test the potential effectiveness of 5-ALA/SFC as adjunctive therapy for patients with MDM receiving insulin therapy. The findings of the study are expected to provide new treatment options for MDM and improve the glycemic control and prognosis of patients with this disorder.

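### The primary endpoint reads insulin secretion from total serum insulin in patients treated with or requiring insulin, so residual injected insulin that differs between the two glucose tolerance tests can imitate or mask a change in secretion

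*Protocol article*

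**What the plan says.** Section 2.4.1 of the protocol article names the quantity of interest as "Changes in glucose-stimulated insulin secretion after the daily administration of 5-ALA/SFC for 24 weeks". The variable that stands for it is "the values of area under the curve of serum insulin levels from fasting (0 minutes) to 120 minutes" in a 75-g OGTT, week 24 against week 0.

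The first main criterion in Section 2.6 admits "Patients with diabetes mellitus being treated with insulin or clinically requiring insulin therapy for glycemic control due to decreased insulin secretion". The Discussion describes the intended use as "adjunctive therapy for patients with MDM receiving insulin therapy".

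On insulin during the trial, Section 2.9 (text after Figure 1) states: "The investigator will refer to the patient's FGM result to adjust the insulin dose based on his/her own judgement". Other antidiabetic agents may not be changed. Section 2.4.2 makes the required daily insulin dose a secondary endpoint.

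Both OGTTs follow an overnight fast, and Section 2.9 adds: "All antidiabetic agents including insulin and 5-ALA/SFC will be held until the preceding day in each OGTT".

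Section 2.10 lists C-peptide next to glucose and insulin at each OGTT: "serum C-peptide (ng/mL), and plasma glucagon (pg/mL) will be measured at fasting (0 minutes) and at 30, 60, 120 minutes". Section 2.4.2 does not name C-peptide; it falls at most under the general item for OGTT values.

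**The concern.** Serum insulin in a person who injects insulin can come from the pancreas or from the syringe. Only the first part is secretion. C-peptide does not have this ambiguity, because injected insulin contains none.

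The endpoint is a within-patient change, so a residual of injected insulin that is the same at both visits cancels. A residual that changes does not, and the plan leaves room for change: insulin is the one antidiabetic treatment that may be altered, and its dose is followed as an outcome. If the residual follows the dose, the direction is unhelpful. Should the product work and the dose fall, a lower residual hides part of the gain. Should the dose rise, a higher residual looks like recovered secretion. A patient who only required insulin at entry and started it later would show the second pattern.

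The trial has one arm, so no comparison group would reveal such a shift. With five patients, one or two dose changes could colour the result on which the hypothesis is judged.

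**Working it through.** The article gives no insulin values, effect size or sample-size derivation, so there is no stated figure to reproduce. The check asks how far a change in residual insulin moves the endpoint.

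**From the article.** Sampling at 0, 30, 60 and 120 minutes (Section 2.10); AUC from 0 to 120 minutes, week 24 against week 0 (Section 2.4.1); n = 5 (Section 2.2).

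**Assumed, for scale only.** Mean endogenous insulin during the OGTT, E = 8, 15 or 25 μU/mL; detected residual injected insulin b0 = 10 μU/mL at week 0 and b1 = 5, 10 or 15 μU/mL at week 24, constant within a test. Endogenous secretion is held unchanged, so any movement is pure distortion.

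**Step 1: absolute shift.** The trapezoidal rule at these times gives weights 15, 30, 45 and 30, which sum to 120. A constant residual b therefore adds 120 × b to the AUC, and a between-visit difference Δ = b1 − b0 shifts the change by 120 × Δ μU·min/mL. For Δ = 1 the shift is 120; for Δ = 5 it is 600. This step does not depend on E.

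**Step 2: relative shift.** Apparent change = (E + b1)/(E + b0) − 1.

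| E (μU/mL) | b: 10 → 10 | b: 10 → 15 | b: 10 → 5 |
|---|---|---|---|
| 8 | 0% | 23/18 − 1 = +27.8% | 13/18 − 1 = −27.8% |
| 15 | 0% | 30/25 − 1 = +20.0% | 20/25 − 1 = −20.0% |
| 25 | 0% | 40/35 − 1 = +14.3% | 30/35 − 1 = −14.3% |

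A smaller move, 8 → 10, gives 18/16 − 1 = +12.5% at E = 8 and 35/33 − 1 = +6.1% at E = 25.

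**Step 3: dependence on the assumed level.** Eligibility rests on reduced secretion, so E may be lower. Three assumed endogenous profiles at 0/30/60/120 minutes:

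- (5, 12, 18, 16): AUC 1725; 120/1725 = 7.0% per 1 μU/mL.
- (3, 6, 8, 7): AUC 795; 120/795 = 15.1% per 1 μU/mL.
- (1.5, 2.5, 3.5, 3): AUC 345; 120/345 = 34.8% per 1 μU/mL.

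These are percentages of the endogenous AUC alone, so they are not on the same base as Step 2. They show that the relative size depends heavily on the assumed level.

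**Step 4: effect on the group mean.** One patient of five with Δ = 5 moves the mean change by 600/5 = 120 μU·min/mL, even if the other four have no shift.

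**The case against.** The strongest reply is that the protocol already deals with injected insulin. All agents including insulin are held before both OGTTs, after an overnight fast. That should rule out an injection on the test morning. What remains is carry-over from earlier doses, and only the part that differs between visits. This stands, and it narrows the concern. It does not close it: the hold sentence can be read as withheld from the preceding day or as continued up to it, and the article gives no interval.

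Second, the percentages rest wholly on assumed inputs. This also stands. They illustrate scale and say nothing about what this trial will show.

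Third, this is a five-patient pilot that plans estimates with 95% confidence intervals, and C-peptide will be available for anyone who wants to compare. That lowers the stakes, but it does not make the chosen primary variable match the stated aim.

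Several stronger readings are tempting and are not supported:

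- A reader might infer that injected insulin will be counted as secretion. Section 2.10 names the assay kit but does not say which insulin products it detects, so only *can be counted* is justified.
- A reader might infer that the distortion vanishes only if the assay misses every product used. The formula in Step 2 is zero whenever b1 = b0, whatever the assay, and also if the hold clears the residual.
- A reader might infer that every participant injects insulin. Section 2.6 also admits patients who clinically require it.
- A reader might add distortion by insulin antibodies. Nothing in the article bears on this.
- A reader might fault the article for not listing insulin types or last-injection times. A condensed article may leave these to the full protocol.

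**Conclusion.** The concern holds as a mismatch between aim and measure. The primary variable is total serum insulin, the population is treated with or requires insulin, the dose may change between the two tests, and no control arm separates a shift in residual insulin from a shift in secretion. The pre-test hold reduces the exposure but is ambiguously worded.

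The absolute size is 120 μU·min/mL of AUC change for each 1 μU/mL of between-visit difference in detected residual, taken as constant over the test. In relative terms the range is 0 to about ±28% for assumed endogenous means of 8 to 25 μU/mL and a residual that moves by 0 to ±5 from 10 μU/mL. Lower endogenous levels would make a given shift proportionally larger. The distortion is nil if the detected residual is equal at both visits, is cleared by the hold or is not detected. The article does not establish any of these three conditions.

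**What to change.** Make C-peptide AUC from 0 to 120 minutes the primary measure of secretion and keep insulin AUC as a supportive secondary. Show creatinine alongside, because C-peptide is cleared by the kidney; creatinine is already measured at every visit (Section 2.10).

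No new sample, visit or assay is needed. The cost lies in the amendment. Version 1.0 is described as final, and the trial was registered in July and August 2020, before publication in March 2021. In an open-label trial, a change of primary endpoint must be dated, justified and decided without sight of outcome data. If outcome data have already been seen, keep insulin AUC as primary and name C-peptide AUC as the key secondary on which any conclusion about secretion depends.

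Separately, reconcile the hold sentence in Section 2.9 so that both OGTTs follow one identical, unambiguous condition. What that condition should be is a clinical decision for the investigators. C-peptide removes injected insulin from the measurement; it does not make up for the missing control group, which the article already lists as a limitation.

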#### Secondary endpoints

2.4.2

Changes in the following items after the daily administration of 5-ALA/SFC for 24 weeks: fasting blood glucose, glycated hemoglobin, glycated albumin, values obtained from the 75-g OGTT, values obtained from the flash glucose monitoring (FGM), and the required daily dose of insulin. For each parameter, any change will be determined based on the difference between the results at baseline (week 0) and those at week 24.

#### Safety endpoints

2.4.3

All adverse events that occurred during the trial will be recorded.

### Participant recruitment

2.5

Participants will be recruited at the Nagasaki University Hospital. The study will be fully explained to potential participants by investigators; participants will then be asked to voluntarily sign an informed consent form before their participation.

### Inclusion criteria

2.6

The study inclusion criteria are as follows:

(1)Patients aged ≥20 years at the time of consent(2)Outpatients(3)Patients diagnosed with MDM who satisfy all of the following main criteria and one or more of the sub-criteria

Main criteria

(1)Patients with diabetes mellitus being treated with insulin or clinically requiring insulin therapy for glycemic control due to decreased insulin secretion(2)Patients complicated with neurosensory deafness

Sub-criteria

(1)Patients who have a family history of maternally inherited diabetes mellitus(2)Patients who show a level of serum lactate ≥ 18 mg/dL (2 mmol/L) and/or a molar ratio of lactate to pyruvate ≥20(3)Patients with short stature whose height is less than –2.0 standard deviation of Japanese adults(4)Patients complicated with cardiomyopathy or cardiac conduction abnormality(5)Patients whose basal-ganglia and brainstem have bilaterally symmetric abnormal lesions on computed tomography/magnetic resonance imaging(6)Patients who have had not changed their antidiabetic agent(s) expect for insulin within 8 weeks before the informed consent is obtained(7)Written informed consent

